### Ethics

This project was registered with the Brazilian Registry of Clinical Trials (ID RBR-9KTWX6).

The project, which is currently in the data collection phase, was approved by the Brazilian Committee of Ethics in Human Research–CONEP (CAAE 30246120.3.1001.5505).

### Statistical Analysis

The data will be analyzed using descriptive statistics—absolute and relative frequencies for categorical variables and quantitative measures (mean, quartiles, minimum, maximum, and standard deviation) for numerical variables. The normality of the data will be verified using the Kolmogorov-Smirnov test.

A chi-square test will be used to assess the association between categorical variables with standardized adjusted residual calculation; Fisher exact test will be used for small samples. The linear associations between two variables of a numerical nature will be evaluated using Pearson correlation.

To evaluate the behavior of clinical variables between two points in time by group, analysis of variance (ANOVA) will be used, with repeated measures. In the case of nonnormality of data, the means of the groups at each time point will be compared using the Kruskal-Wallis nonparametric test. To compare the means between phone visits in each group, the Wilcoxon nonparametric test will be used.

The comparison between the means of numerical variables with normal distribution will be verified through the Student *t* test. If the assumption of normality is violated, the Mann-Whitney nonparametric test will be used.

Adjusted multiple linear regression models will be used to assess the simultaneous effects of sex, age, duration of illness, comorbidities, concomitant medications, and other confounding variables, according to group and predefined outcomes. For dichotomous dependent variables, a logistic regression model will be preferred. Survival analysis models, including log rank and Kaplan-Meier tests, adjusted for confounding variables, will be developed to assess the main outcomes over time. The time defined as the end date will be the date of a major event, such as illness with confirmation or suspicion of infection, hospitalization, or death.

Correlation analysis will be performed using the Pearson test to assess the relationship between the incidence rate of confirmed COVID-19 cases per 100,000 inhabitants and the proportion of symptomatic patients and controls in municipalities. Data of confirmed cases per municipality are available through the Brasil.io project [51]. The QGIGS Desktop 3.6.0 (Open Source Geospatial Foundation) will be used for map plotting.

SPSS, version 20 (IMB Corp) will be used in all analyses, and a *P* value <.05 will be considered significant.

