### Sample Size

Considering a moderate-to-severe COVID-19 rate as the dependent variable, a rate which the current literature estimates to be 20% [4,6,10-18,40-42] as well as the proportion of 1 case for every 2 controls, the sample calculation was approximately 3000 antimalarial users and 6000 nonusers, with an error α=5% and β=20%.

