## Results

This study is in the data collection phase. Study recruitment opened in March 2020. In an 8-week period (from March 29 to May 17), a total of 10,443 individuals enrolled at baseline (including 5166 patients with rheumatic diseases) from 23 tertiary rheumatology centers in 97 Brazilian cities. Data analysis is scheduled to start after all relevant data have been collected.

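### For numeric variables followed in both groups, a Kolmogorov-Smirnov gate that will usually reject at thousands per group leads to a fallback with no test of whether the groups change differently (minor)

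*Protocol article*

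**What the plan says.** All of this stands in the Statistical Analysis section of the protocol article.

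- Gate: "The normality of the data will be verified using the Kolmogorov-Smirnov test". No graphical check, size-of-departure criterion or large-sample exception accompanies it.
- Method if the data pass: "To evaluate the behavior of clinical variables between two points in time by group, analysis of variance (ANOVA) will be used, with repeated measures".
- Between-group method if they fail: "In the case of nonnormality of data, the means of the groups at each time point will be compared using the Kruskal-Wallis nonparametric test".
- Within-group method: "To compare the means between phone visits in each group, the Wilcoxon nonparametric test will be used". The text can be read as applying this only under non-normality or in every case.
- Significance: "a *P* value <.05 will be considered significant".

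The same section plans linear and logistic regression and survival models, adjusted for confounders. It names no visit term and no group-by-visit term in any of them. On size, the Results section reports "a total of 10,443 individuals enrolled at baseline (including 5166 patients with rheumatic diseases".

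**The concern.** A normality test answers whether a departure can be detected, not whether it matters. Its power grows with sample size, while the harm that a given departure does to a comparison of means shrinks. With groups in the thousands, the gate therefore tends to reject just where normality is least needed, and the fallback becomes the working analysis.

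The fallback also answers a different question. Repeated-measures ANOVA by group contains a group-by-time term. With two groups, Kruskal-Wallis at one visit is a cross-sectional rank comparison equivalent to Mann-Whitney. Wilcoxon within a group asks whether that group moved. Neither is a test of means, although the article uses that word for both, and neither asks whether one group moved more than the other. At stake is the validity of any statement about differential change in a numeric variable recorded at several interviews in both groups.

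**Working it through.** **Inputs from the article.** Enrolled 10,443, of whom 5166 are patients, so 10,443 − 5166 = 5277 others, taken here to be the controls. Significance level 0.05. The article states no figure for the behaviour of the gate or the fallback, so there is none to reproduce. The sample-size figure plays no part in this point.

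**Assumptions.** The article gives no distributions, standard deviations (SD) or within-person correlations. Those below are assumed. It also does not say whether the Kolmogorov-Smirnov critical value allows for an estimated mean and SD (Lilliefors), so both versions are shown.

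**Step 1: how tight the gate becomes.** The uncorrected 5% limit is 1.358/√n: 0.1358 at n=100 and 0.0192 at n=5000. The simulated Lilliefors limits are 0.0895 and 0.0131. The tolerated departure falls about sevenfold (√(5000/100) = 7.1).

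**Step 2: how often the gate rejects** (1000 runs each).

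| Data | n=100, Lilliefors / uncorrected | n=5000, Lilliefors / uncorrected |
|---|---|---|
| Exactly normal | 4% / 0% | 3% / 0% |
| Skewness 0.2 | 6% / 0.2% | 94% / 38% |
| Skewness 0.3 | 10.5% / 0.1% | 99.9% / 93% |
| Skewness 0.5 | 24% / 0.3% | 100% / 100% |
| Integer 0–10 scale | 100% / 33% | 100% / 100% |

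At n=5000, skewness 0.3 in the data leaves skewness of only 0.3/√5000 = 0.004 in the sample mean. That has no practical effect on a comparison of means.

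**Step 3: what the fallback can tell apart.** Two visits were simulated with 5166 and 5277 people, SD 1, within-person correlation 0.6 and 500 runs. The group-by-time test is a t test on change, which equals the ANOVA interaction for two visits. Both scenarios have a baseline difference of 0.2 SD.

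| True change, patients / controls | Kruskal-Wallis, each visit | Wilcoxon, each group | Group-by-time |
|---|---|---|---|
| −0.2 / −0.2 SD (equal) | 100%, 100% | 100%, 100% | 6.6% |
| −0.3 / −0.2 SD (unequal) | 100%, 100% | 100%, 100% | 100% |

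The four fallback tests give the same pattern whether or not the groups change differently. The direct test separates the two cases.

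**Step 4: would contrasting the two Wilcoxon results mislead?** If both groups change equally and each test has power p, exactly one is significant with probability 2p(1−p).

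- The SD of change is √(2(1−0.6)) = 0.894, and the standard error in patients is 0.894/√5166 = 0.0124.
- Change of 0.025 SD: simulated power was about 0.5 per group. The formula gives 2×0.5×0.5 = 50%, the simulation 51%, and the interaction test rejected in 5.4%.
- Change of 0.05 SD: 0.05/0.0124 is about 4.0, so power is about 0.975 to 0.98. Discordance is 2×0.975×0.025 = 4.9% down to 2×0.98×0.02 = 3.9%.
- Change of 0.1 SD: practically zero.

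Frequent false contrasts at this size therefore need a change close to 0.025 SD.

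**The case against.** The strongest objection is about reach. Moderate-to-severe disease is defined by hospitalization, mechanical ventilation or death, so progression to it is categorical. The plan sends dichotomous outcomes to logistic regression and the main outcomes over time to survival models, and neither passes through the gate. Disease activity belongs to rheumatic patients only, and length of stay to hospitalized people only. The article names no numeric variable that is clearly measured repeatedly in both groups at about 5000 each, and missed interviews lower the numbers further. All of this stands and limits the weight.

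A reader might infer that the stated secondary outcomes, on course severity and progression between groups, rest on the flawed fallback. The documents do not show that: progression is categorical, and no numeric measure of course severity is specified.

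A reader might also infer that false group differences will be common, because significance in one group and not the other would be read as a difference. The plan nowhere says it will draw that inference, and Step 4 shows that at this size the problem is frequent only for negligible changes. Nor would failure of the gate by a baseline variable such as age be evidence here. Age never enters the between-visit comparison, and it would simply move from a t test to Mann-Whitney.

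Confounding is addressed by the adjusted models planned alongside, so the rank tests' lack of adjustment is not by itself a gap in the plan. Those models name no visit or group-by-visit term, however, so they do not clearly restore the lost comparison.

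Finally, model details are often left to a fuller document. That does not remove the point, because the article itself states the gate and the replacement tests.

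**Conclusion.** The point holds for numeric variables measured repeatedly in both groups, and its weight is minor. For these, the stated gate will usually reject at thousands per group for departures that do not matter: 93% to 99.9% of runs at skewness 0.3 and n=5000. This is not a certainty. The rate is 38% with the uncorrected limit at skewness 0.2 and about nil to 3% for exactly normal data, and at n=100 mild skewness seldom triggers it. Once it rejects, the plan loses its only stated test of differential change and keeps tests that do not compare means as described.

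The loss of that test follows from the text alone. The rejection rates rest on assumed distributions, and the fallback comparison on an assumed SD of 1 and correlation of 0.6. If the Wilcoxon sentence applies whether or not the data are normal, the conclusion is the same. The main outcomes and progression to moderate-to-severe disease are unaffected.

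**What to change.** Drop the Kolmogorov-Smirnov gate for the longitudinal comparisons of numeric variables. Name one mixed model for them, with group, visit, group-by-visit and the confounders already listed under Outcomes (age, sex, comorbidities, concomitant medications, flu vaccine). Use robust standard errors or a transformation where a variable is skewed, and read the difference in change between groups from the interaction. Keep any Kruskal-Wallis and Wilcoxon tests as descriptive only, and stop describing them as comparisons of means. It would also help to list the variables to which this applies.

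The cost is revised analysis wording and slightly more work. No new data are needed, and the article reports the study as still in data collection, with analysis to follow.

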### Control Group

The control group will consist of healthy individuals aged >18 years, who are household cohabitants or work colleagues of patients with rheumatic diseases in the intervention group.

Contact with a suspected or confirmed case of COVID-19 is defined as an individual sharing accommodations with a patient with a rheumatic disease (eg, residing in the same house or environment as roommates, occupational colleagues, etc). The exposure grade assessment is individualized, considering the type of environment and the exposure time.

For each case, two household and/or professional contact individuals will be selected as controls. The choice of the first control is prioritized by flu-like symptoms and defined as the “symptomatic group,” including suspected or confirmed cases. Those without symptoms will comprise the “asymptomatic group;” both household and/or contact individuals can be selected, preferably paired for age and sex.

The household and/or workplace contacts were chosen to characterize the control group because of their high epidemiological value during community viral transmissions worldwide, instead of including nonusers of antimalarials with rheumatic diseases. Moreover, lupus patients without antimalarial treatment are quite uncommon, except in those with previous toxicity (maculopathy, allergy, long-term remission, etc).

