**Figure 3 figure3:**
[figure not shown]
Suspected vs confirmed cases of COVID-19. RT-PCR: real-time polymerase chain reaction, IgM: immunoglobulin M, IgA: immunoglobulin A, IgG: immunoglobulin G, ELISA: enzyme-linked immunosorbent assay, IC: ion channel, ECLIA: electrochemiluminescence immunoassay.

Moderate-to-severe cases are defined as those that require hospitalization, mechanical ventilation, or result in death. Through direct contact with hospitals, hospitalized patients are being clinically evaluated in terms of longitudinal follow-up and treatment outcome, infection severity, length of stay, need for intensive care, mechanical ventilation, and cause of death.

Considering the heterogeneous community viral transmission in Brazil, some epidemiological approaches were developed to assure a similar path involving patients with rheumatic diseases and controls, such as the same pandemic COVID-19 curve in each city and region [41]. Therefore, after initial contact (V1), two strategies were adopted to maintain the follow-up of patients and to optimize the capture of main outcomes. Firstly, an active strategy is addressed in cases of flu-like syndrome and symptoms suggestive of COVID-19. For this strategy, the patient or household member is shown how to provide clinical data on the patient or his/her control through a toll-free telephone number (the 0800 system). Secondly, the patient is contacted every week by the REDCap team to gather relevant data on infection. An additional visit is conducted if the patient or control provides information about flu symptoms or disease activity via an unscheduled phone call or contact through the toll-free number. In both cases the individual will be advised to stay home and use painkillers or an antipyretic. In case of worsening/severe symptoms (eg, persistent cough or fever and shortness of breath), they will be advised to visit a hospital or to make an appointment with a physician involved in our study.

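### Controls are chosen patient by patient, but every named patient-control analysis treats people as independent, so the contrast's standard error is too wide by an unknown amount, and the named survival methods cannot make the stated adjustment

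*Protocol article*

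**What the plan says.** The Control Group section of the protocol article ties each control to one patient: "For each case, two household and/or professional contact individuals will be selected as controls". Controls are cohabitants or work colleagues, and pairing on age and sex is a preference, not a requirement. The Data Collection section (text after Figure 3) gives the aim of its follow-up measures as: "to assure a similar path involving patients with rheumatic diseases and controls, such as the same pandemic COVID-19 curve in each city and region". Shared local exposure within a set is therefore intended.

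The Statistical Analysis section names these methods:

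- Categorical variables: "A chi-square test will be used to assess the association between categorical variables with standardized adjusted residual calculation", with Fisher's exact test for small samples.
- Numerical variables: Student t or Mann-Whitney.
- Binary outcomes: "For dichotomous dependent variables, a logistic regression model will be preferred".
- Time to event: "Survival analysis models, including log rank and Kaplan-Meier tests, adjusted for confounding variables, will be developed to assess the main outcomes over time".

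Repeated-measures ANOVA and the Wilcoxon test also appear, but for changes between visits, not for comparisons within a patient-control set. No conditional, set-stratified, mixed, GEE, frailty or cluster-robust method is named. The adjustment variables in the Outcomes section are age, sex, comorbidities, concomitant medications and flu vaccination; neither set nor household is among them.

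**The concern.** The sampling unit is a patient with their own controls, but the analysis as written takes the individual as the unit. People who share a home or workplace plausibly share infection risk. If so, the variance that an independent-samples method attaches to the patient-control difference is not the true one. At stake are the width of the confidence interval and the P value for the main comparison, in a study whose hypothesis is a protective effect.

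The survival sentence has a separate fault. Kaplan-Meier is an estimator, not a test. The log rank test can be stratified by a few categories but does not adjust for a list of covariates of this kind. No regression model that could do so is named for time to event.

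**Working it through.** **The plan's own figure.** The Sample Size section gives a rate "a rate which the current literature estimates to be 20"%, "the proportion of 1 case for every 2 controls", "with an error α=5% and β=20"%, and about 3000 users and 6000 nonusers. It states no second rate and no within-set correlation, so the figure cannot be strictly reproduced. Solving backwards with the usual two-sided formula for two proportions at 1:2, it fits 20% against about 17.55%, a difference of 2.45 points:

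- Pooled rate = (0.1755 + 2 × 0.20)/3 = 0.1918.
- n = [1.96 × sqrt(1.5 × 0.1918 × 0.8082) + 0.8416 × sqrt(0.1755 × 0.8245 + 0.16/2)]² / 0.0245² = 3010 users.

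This back-solved difference is used below only to express the effect as power.

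**Variance of the contrast.** Take sets of one patient and k controls, a common outcome variance s² and a common within-set correlation rho.

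- Var(mean of k controls) = s²[1 + (k-1)rho]/k.
- Cov(patient, mean of controls) = rho × s².
- Var(patient minus mean of controls) = s² + s²[1 + (k-1)rho]/k - 2 × rho × s² = s²(1 + 1/k)(1 - rho).
- An independent-samples method uses s²(1 + 1/k).

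The standard error used is therefore 1/sqrt(1-rho) times the true one, whatever k is. The true size of a nominal 5% test is 2 × [1 - Phi(1.96/sqrt(1-rho))].

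**Results.** rho is assumed. Power is for 3000:6000 and the 2.45-point difference.

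| rho | SE too wide by | True size | Power, independent-samples test | Power, set-based test |
|---|---|---|---|---|
| 0 | 0% | 5.0% | 80.0% | 80.0% |
| 0.05 | 2.6% | 4.4% | 80.6% | 82.0% |
| 0.1 | 5.4% | 3.9% | 81.3% | 84.0% |
| 0.2 | 11.8% | 2.8% | 82.7% | 88.0% |
| 0.3 | 19.5% | 1.9% | 84.3% | 91.9% |

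At rho 0.02, the same formulas give a standard error about 1% too wide and a size of about 4.8%.

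**Simulation check.** With 3000 sets of 1:2, a 20% rate and 4000 runs under no effect, the independent-samples test rejected in 4.1%, 2.5% and 1.8% of runs at rho 0.1, 0.2 and 0.3. The set-based test rejected in 5.3%, 4.7% and 4.9%.

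**Enrolled ratio.** The Results section reports 10,443 people, of whom 5166 are patients. That leaves 10,443 - 5166 = 5277 others, or 5277/5166 = 1.02 per patient instead of two. Simulating 5166 pairs gave rejection rates of 4.0% at rho 0.1 and 1.9% at rho 0.3, so the result does not depend on the 1:2 ratio.

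**Direction.** The conservative direction applies to the patient-control contrast only. For the rate among controls alone, with two controls per set, the variance is multiplied by 1 + rho, so an interval that ignores the set is too narrow.

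**The case against.** Four points on the other side have weight.

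- **rho may be small.** The documents give no value. The primary aim concerns hospitalization, ventilation or death, which may be only weakly correlated within a set, and some controls are colleagues and not cohabitants. This stands, and is why the range starts at 0.
- **The error is conservative and planned power is not breached.** This also stands. In the table, the independent-samples test stays at or above 80%. The loss is relative to an analysis that uses the sets.
- **The formula is idealised.** It assumes complete sets and one common correlation. Enrolment near 1:1 means that some sets may not have two controls, and the first control is prioritised for flu-like symptoms. Set-based analysis does not repair that selection.
- **The article is condensed.** The word including leaves the survival models open, and a fuller plan might specify clustering. But the article commits to particular methods, and those named do not fit the sampling it describes.

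Two stronger readings are tempting. A reader might infer that the matching is wasted. It is not: choosing controls per patient still largely balances shared exposure in a crude comparison, to the extent that sets are complete, and age and sex are adjusted for in any case. A reader might also infer that an ordinary logistic model gives a biased odds ratio because it lies closer to 1 than the set-conditional one. That gap is non-collapsibility, a difference of estimand. It is small for rare outcomes, and a GEE model shares it.

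**Conclusion.** The mismatch between design and analysis is real and should be corrected. For the patient-control contrast, the standard error is too wide by 1/sqrt(1-rho): from 0% to 20% over an assumed rho of 0 to 0.3, with the true size of a 5% test falling from 5% to 1.9%. Outcomes such as hospitalization or death probably sit near the low end, and infection higher. The consequence is lost precision and a greater chance of missing a protective effect, not a false claim of one. The size rests on the assumed rho, complete sets and a common correlation. The statement that log rank and Kaplan-Meier are adjusted for confounders is wrong for this covariate list whatever rho is.

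**What to change.** Keep a patient-control set identifier in the dataset and rewrite the analysis text as follows.

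- **Binary outcomes:** GEE logistic regression clustered on the set, which keeps everyone, with conditional logistic regression as a sensitivity analysis.
- **Time to event:** Cox regression with set-robust standard errors, or stratified by set.
- **Adjustment:** use the covariates listed under Outcomes in both models.
- **Description:** keep chi-square, Kaplan-Meier and log rank as unadjusted summaries, and delete the statement that the last two are adjusted.

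The cost is one identifier and some wording; the article says that analysis is still to start. Conditional and set-stratified models use only informative sets, and the conditional odds ratio is a different estimand from the marginal one, so the plan should say which is primary. The plan also names a single software package for all analyses, so check that it fits the chosen models before the wording is fixed.

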**Figure 1 figure1:**
[figure not shown]
Centers participating in the study.

All patients and controls gave a verbal informed consent before participating in this cohort study. The need for signed informed consent was waived by the Brazilian National Ethics Committee (CONEP) due to the urgency of the pandemic. However, it is worth emphasizing that participation was voluntary for both groups. Research subjects will not be identified by their full name at any time and will not have their personal data disclosed.

The data are being stored on the REDCap platform, with telephone interviews performed as shown in Figure 2. Interviews with patients with invalid contact information or who did not answer the telephone after three consecutive calls at intervals of 3 days were canceled, although patients were not removed from the study. All patients will be evaluated during the closing visit (V6), unless they decline to participate, regardless of whether intermediary visits were missed (V2 to V5).

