## Discussion

This study’s novel design, with its large sample of chronic antimalarial users, will enable us to perform a thorough prospective assessment (every 2 weeks) to explore whether vulnerability to SARS-CoV-2 infection may be associated with IMRD or to hydroxychloroquine after adjustments for cofounders, especially those related to other immunosuppressive drugs and comorbidities. On the other hand, it has some limitations, such as compliance and adherence; a potential shortage of HCQ (hydroxychloroquine) in some parts of our country; possible biases associated with recalling symptoms; inability to answer the phone (due to hospitalization or death), and lack of confirmatory tests (PCR tests for SARS-CoV-2 or antibody-based RNA [ribonucleic acid]) for all enrolled patients and controls, especially in those with nonsevere forms. Future randomized controlled trials may provide a better understanding of these differences.

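### Repeated-measures ANOVA between two visits leaves out anyone missing either visit, although the protocol expects missed interviews and keeps those people in the study

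*Protocol article*

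**What the plan says.** The method is in the Statistical Analysis section. For the course of clinical variables from one time point to another, by group, "analysis of variance (ANOVA) will be used, with repeated measures". If the data are not normal, "the means of the groups at each time point will be compared using the Kruskal-Wallis nonparametric test". For change within a group, "To compare the means between phone visits in each group, the Wilcoxon nonparametric test will be used". The section names SPSS version 20 for all analyses. It assigns dichotomous variables to logistic regression and the main outcomes over time to survival models.

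The follow-up rule is in Data Collection. Interviews with people who could not be reached after three calls "were canceled, although patients were not removed from the study". The closing visit V6 is sought from everyone who does not decline, "regardless of whether intermediary visits were missed (V2 to V5".

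The reason for some of the non-response is in the Discussion, which lists among the limitations "inability to answer the phone (due to hospitalization or death".

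**The concern.** The follow-up rule and the analysis method pull in different directions. Follow-up keeps a person who misses a call. Standard repeated-measures ANOVA works on complete within-person sets, so it drops that person from any comparison that uses the missed visit, and the measurement that was obtained at the other visit is dropped too.

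Two things are at stake. One is precision, because completed interviews go unused. The other is possible bias: if people fail to answer because they are in hospital or have died, those left in the comparison are on average less ill than those enrolled. The comparisons exposed are those of numerical clinical variables between visits, which at most feed the secondary outcomes on clinical course.

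**Working it through.** The plan gives no figure for this point, so there is nothing to reproduce. The check has two parts.

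**1. How many people are lost**

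Inputs: 10,443 enrolled, of whom 5166 are patients (Results). The missed-call rate m is not in the article; 5%, 10% and 20% are assumed, equal in both groups. V1 is taken as complete because everyone enrolled at baseline.

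- V1 against one follow-up visit: loss = m.
- Two follow-up visits with independent misses: loss = 1 − (1 − m)².

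| m | V1 v one follow-up visit | People | Two follow-up visits | People |
|---|---|---|---|---|
| 5% | 5% | 522 | 1 − 0.95² = 9.75% | 1018 |
| 10% | 10% | 1044 | 1 − 0.90² = 19% | 1984 |
| 20% | 20% | 2089 | 1 − 0.80² = 36% | 3759 |

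If the same people tend to miss both calls, the two-visit loss is smaller, down to m.

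**2. Whether the loss can bias the comparison**

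Every input here is assumed and serves only to show direction. Severe cases are a share s = 3% of patients and 5% of controls, and are 2 SD worse on a change score. Non-severe people miss the visit at 10%, severe people at rate q. The true group difference is 2 × (0.05 − 0.03) = 0.040 SD.

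Among complete pairs the severe share is s(1 − q) / [s(1 − q) + (1 − s) × 0.90], and the group difference is twice the difference in these shares.

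- q = 10%: shares 0.05 and 0.03; difference 0.040.
- q = 30%: 0.035/0.890 and 0.021/0.894; difference 0.032.
- q = 50%: 0.025/0.880 and 0.015/0.888; difference 0.023.
- q = 80%: 0.010/0.865 and 0.006/0.879; difference 0.009.

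A simulation with the enrolled group sizes gave 0.041, 0.030, 0.023 and 0.010, in agreement. With equal miss rates there is loss of information but no bias. Bias appears only when missing a call depends on severity, and its size depends on rates that the article does not give.

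**The other tests in the same paragraph.** Kruskal-Wallis at each time point uses whoever answered at that visit, so it does not delete by pairs, but it still lacks that visit's non-responders. The Wilcoxon test between visits, if it is the paired test, has the same deletion as the ANOVA.

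**The case against.** The strongest reply has four parts.

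- *The ANOVA is narrow.* It is planned for two time points only, and V6 is sought from everyone, so a V1 to V6 comparison is not harmed by missed calls in between. This stands. Only a missing visit within the compared pair matters, although people who have died or declined have no V6.
- *Severe disease is captured elsewhere.* Data Collection describes direct contact with hospitals, a toll-free line open to household members, weekly contact and extra visits when symptoms are reported. This stands too, and it may recover some of what the scheduled calls miss. The article does not say that such data would fill a missed visit in the ANOVA.
- *Missing-data handling belongs in an analysis plan that is not shown.* This would answer a complaint that no missing-data policy is given. It does not answer a mismatch between a method that the article fixes and a follow-up rule that it also fixes. It is fair to add that the article neither states nor rules out imputation.
- *A mixed model does not cure outcome-related non-response.* This is right. It rests on missing at random and does not by itself handle truncation by death. An ordinary unweighted GEE needs stronger assumptions still and should not be offered as the answer.

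A reader might infer that the sickest participants vanish from the study's main comparisons and that progression is therefore understated. The documents do not support this. Data Collection defines moderate-to-severe disease by hospitalization, mechanical ventilation or death, and such outcomes go to logistic or survival models. A reader might also work out a larger loss by requiring all follow-up calls to be complete, but the article plans no such analysis.

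**Conclusion.** The concern holds as a minor one. For numerical clinical variables compared between two visits by group, the stated method discards people whom the protocol keeps. The loss is 5% to 20% for V1 against one follow-up visit, and about 10% to 36% for two follow-up visits, if 5% to 20% of calls are missed and, in the second case, misses are independent. The actual rate is not given.

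A lean towards less ill participants is plausible, because the Discussion ties some non-response to hospitalization or death. It remains an inference of unknown size. Hospitalization, intensive care, ventilation, death and progression defined by them are outside its reach.

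**What to change.** Replace repeated-measures ANOVA with a linear mixed model for each numerical clinical variable, with group, visit and group-by-visit terms, baseline predictors of severity and non-response, and every completed interview included. The covariates that the Outcomes section already lists for adjustment, such as age, sex, comorbidities and concomitant medications, are natural candidates. Read the planned two-visit comparison from the group-by-visit term.

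Add a sensitivity analysis for non-response related to hospitalization or death, for example by varying the assumed values of those who could not answer for these reasons, and say how people who died before the compared visit are treated. Report the number of interviews completed by group and visit.

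The cost is a change of wording and a little analysis work. Mixed models are available in the planned software, no new data are needed, and the article says that analysis has not begun. The mixed model's own assumption of missing at random remains, which is why the sensitivity analysis belongs with it.
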